# Nursing home care educational intervention for family caregivers of older adults post stroke (SHARE): study protocol for a randomised trial

**DOI:** 10.1186/s13063-018-2454-5

**Published:** 2018-02-09

**Keywords:** Randomized controlled trial, Nursing, Stroke, Aged, Caregivers, Home care services

## Abstract

**Background:**

Family caregivers of aged stroke survivors face challenging difficulties such as the lack of support and the knowledge and skills to practice home care. These aspects negatively influence the caregivers’ burden and quality of life, the use of health services, and hospital readmissions of the stroke survivor. The aim of this research is to describe an educational intervention focused on family caregivers of stroke survivors for the development of home care in the south of Brazil.

**Methods:**

A randomized clinical trial with 48 family caregivers of stroke survivors will be recruited and divided into two groups: 24 in the intervention group and 24 in the control group. The intervention will consist of the systematic follow-up by nurses who will perform three home visits over a period of 1 month. The control group will not receive the visits and will have the usual care guidelines of the health services. Primary outcomes: burden and quality of life of the caregiver. Secondary outcomes: functional capacity and readmissions of the stroke survivors; the use of health services of the stroke survivors and their family caregivers. Outcomes will be measured 2 months after discharge. The project was approved in April 2016.

**Discussion:**

This research offers information for conducting educational intervention with family caregivers of stroke survivors, presenting knowledge so that nurses can structure and plan the actions aimed at the education of the family caregiver. It is expected that the educational intervention will contribute to reducing caregiver burden and improving their quality of life, as well as avoiding readmissions and inadequate use of health services by stroke survivors.

**Trial registration:**

ClinicalTrials.gov, ID: NCT02807012. Registered on 3 June 2016. Name: Nursing Home Care Intervention Post Stroke (SHARE).

**Electronic supplementary material:**

The online version of this article (10.1186/s13063-018-2454-5) contains supplementary material, which is available to authorized users.

## Background

Stroke is the third leading cause of death in developed countries and the second in developing countries such as Brazil [1]. In the southern region of the country, this disease presents the highest rates of hospital admissions [2]. In older adults, stroke is the second cause of death and the most prevalent cerebrovascular disease [1].

In Brazil, approximately 50% of older adults affected by stroke survive. These adults require assistance for daily activities and they are cared for by their own family at home [3]. The family caregivers face difficulties related to the instrumental, emotional and financial support and also the lack of knowledge and skills to perform the activities of care [4]. Support programs for caregivers after hospital discharge have demonstrated beneficial effects when structured in training interventions for family caregivers so that stroke survivors can receive proper care at home [5, 6]. These interventions are associated with the reduction of the caregiver’s burden and the improvement of their quality of life (QofL) [7, 8].

A structured model of home care for caregivers of stroke survivors after hospital discharge is non-existent in Brazil. However, because of the aging population and the need to reduce hospital costs, it is necessary to discuss national health policies directed toward home care [9].

Currently, discharge planning with adequate transition of care is not a reality in most hospital institutions and the patients return home without receiving adequate orientation and information on post-discharge care. These aspects may leads to major risks for readmission in hospitals and demands on the emergency services [9–12].

In Brazil, the home care policy determines that the health professionals, who are part of the home care teams, provide assistance for the users, being responsible for training the caregivers and involving them in the care [13, 14]. However, although Brazilian public health policies define the formation of a health care network, they present fragility, lack of transition of care and inefficient health services in home care for stroke survivors and their caregivers [15]. As a consequence, the responsibility for the care of stroke survivors rests with the family and with an informal network of community members.[16].

Care and assistance for daily life activities of the stroke survivors is often unexpected. Family members in this situation suddenly find themselves without previous training [15, 17, 18]. This context contributes to the high level of caregiver burden [3], also influencing the worsening of their QofL [19]. Furthermore, without guidance, care for the aged cannot be expected to be understood and performed correctly by the caregiver [20], contributing to the consequent hospital readmissions of the older adults and the complications of negligent home care [21].

The acquisition of knowledge by the caregiver is not arbitrary, but rather acquired through the guidance of a health professional at the time of hospital discharge or when returning to the community [3]. Some studies have described models of educational intervention directed to caregivers of stroke survivors at home after discharge, using telephone or educational groups conducted by nurses or multidisciplinary teams [8, 22–24]. They focus on the training of technical skills for care, resulting in beneficial results for the older adults and their caregivers [5, 25].

An integrative review of Brazilian studies on family caregivers of the aged proposes interventions of social, emotional and psychological support as a form of assistance and improvement of the QofL of the caregivers at home [26]. In home care, the nurse is the professional who has the skills to educate the family caregiver of the stroke survivor in the face of this new reality [27]. In addition, it plays a fundamental role in the orientation and education of these patients and their families, both at the time of hospital stay and when discharged to return home.

This research offers information for conducting educational intervention with family caregivers of stroke survivors, presenting knowledge that nurses can structure and plan the actions aimed to the education of the family caregiver, as well as to assist them in their care activities. In addition, it shows that the adequate preparation of these caregivers positively influences their burden and QofL, as well as avoiding hospital readmissions or inadequate use of health services.

The protocol offers support for the strengthening and effective implementation of home care services (HCS) as a modality of care. Moreover, it can be used by hospital transition teams that continue home care after discharge, in an attempt to avoid rehospitalization; by primary care services, in which physicians and nurses make home visits (HVs) to the families; and in the support of HCS already structured or structuring.

## Methods

### Aim

To describe an educational intervention focused on family caregivers of the stroke survivors for the development of care at home (SHARE) in the south of Brazil.

### Objectives of the research

To determine the effect of the SHARE intervention on the burden of care and QofL of family caregivers of stroke survivors compared to conventional careTo evaluate the stroke survivors’ hospital readmissions and the use of the health services by them and their caregivers after the SHARE intervention

### Hypotheses

The family caregivers who will receive the intervention will have a better QofL and less burden when compared to the caregivers allocated in the control group (CG)The stroke survivor in the intervention group (IG) will present greater functional independence and will have fewer hospital readmissions and use of health services than those in the CG

### Design

A randomized controlled trial (RCT), blinded and with follow-up (2 months after hospital discharge), designated Nursing Home Care Intervention Post Stroke (SHARE). All stages of the RCT are in accordance with the recommendations of the Consolidate Standards of Reporting Trials (CONSORT) [28]. The protocol study is in accordance with the Standard Protocol Items: Recommendations for Interventional Trials (SPIRIT) Checklist as Additional file 1 and Fig. 1.

**Fig. 1 Fig1:**
[figure not shown]
Schedule of enrollment, interventions and assessments of the SHARE intervention

### Setting

The locale of recruitment of the participants is the Special Care Unit of Stroke (SCU-Stroke) at a university hospital in the south of Brazil. The SCU is intended to serve patients with a diagnosis of stroke and is part of a clinical hospitalization unit where approximately 10 beds are allocated to stroke patients. In this unit, they are followed up by a multidisciplinary team that provides care information according to the needs of patients and their families. The intervention and follow-up of the participants will be carried out in the homes of the stroke survivors.

### Participants

The study participants will be the family caregivers selected at the time of hospital discharge at the SCU-Stroke. Family caregivers will be considered the persons responsible for the care of the stroke survivor at home. They will reorganize the home for the stroke survivor and perform most of the care. They may or may not have consanguineous ties with the stroke survivor.

### Inclusion criteria

Participants will be included if they meet the following criteria: (1) to be a family caregiver of the aged (60 years old or more) stroke survivor with the first functional sequel from the SCU-Stroke; (2) stroke survivor with a minimum score of 2 on the Modified Rankin Scale (mRankin) at the time of discharge; (3) family caregiver 18 years or older; (4) a family caregiver who provides unpaid care and (5) stroke survivor who resides in the city of the study or another city within a distance of 20 km from the hospital.

### Exclusion criteria

Participants will be excluded if: (1) the stroke survivor resides in a long-term institution; (2) the stroke survivor is included in an HCS; (3) the stroke survivor died during the study and (4) the family caregiver is not interested in participating in the SHARE intervention.

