### Recruitment and randomization

The stroke survivors and their family caregivers will be selected during the hospital stay at SCU-Stroke. Those who meet the inclusion criteria and are eligible will be invited to participate in SHARE. Ethical procedures will be guaranteed and participants will be able to discontinue participation at any time in the research. Participants selected will receive a HV for baseline assessment within 7 days after discharge. Participants will be picked up, selected and evaluated by research assistants, who in order to minimize bias, will be responsible for: (1) obtaining the consent of family caregivers and the stroke survivors and (2) sending the participants baseline data for randomization.

The allocation of the participants in the IG or in the CG will be through simple randomization, through a numerical list generated by the website randomization.com. This list has a numerical order, in which each number is already assigned to one of the groups randomly. Thereafter, patients are given a number and their designation as they are included in the study. Randomization will occur after the baseline evaluation of stroke survivors and family caregivers, and will be performed by a trained research assistant who is not involved in the evaluation of the participants nor involved in the SHARE intervention.

The CG will receive conventional care, and the IG will receive the SHARE intervention. The assistant responsible for randomization will inform the interventional nurses which patients are assigned to the IG. The final evaluation of all participants will be performed by the same research assistants in the initial assessment 60 days after the date of the patient’s discharge from the hospital. The logistics of the study are presented in Fig. 2. Regarding the blindness, the trial will have outcomes obtained from blinded evaluators. Study participants will not be blind to the intervention.

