### Data collection and outcomes

#### Primary and secondary outcomes

The primary outcomes will be: the caregiver’s burden and QofL, as measured by the Caregiver Burden Scale and by the World Health Organization Quality of Life–BREF (WHOQOL-BREF)_ and the World Health Organization Quality of Life (for caregivers aged over 60 years) (WHOQOL-OLD) [32–34]. Secondary outcomes: functional capacity measured by Functional Independence Measure (FIM) [35]; the hospital readmission of the stroke survivors and the use of health care services by participants after the stroke episode. Primary outcomes and functional capacity will be measured within 1 week after discharge and 2 months after discharge. The outcomes of hospital readmission and use of health services will be evaluated 60 days after discharge (Table 1).

**Table 1 Tab1:** Outcomes and time of data collection: stroke survivors and their family caregivers

Outcome and instrument	Family caregiver vs. stroke survivors	Data collection time	
		T0 (7 days)	T1 (60 days)
Primary outcomes			
Caregiver Burden Scale	Family caregiver	X	X
World Health Organization Quality of Life (WHOQOL-BREF and -OLD)	Family caregiver	X	X
Secondary outcomes			
Functional Independence Measure (FIM)	stroke survivor	X	X
Hospital readmission (yes/no)	stroke survivor		X
Use of health care services	Family caregiver and stroke survivor		X

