### Data analysis

The analysis will be performed by intention-to-treat, where data from all participants (stroke survivors and their family caregivers) will be used regardless of the time they participated in the study [46]. Quantitative variables will be expressed as means and standard deviations or median and interquartile range. The Shapiro-Wilk test will be used to assess the distributions of the continuous outcomes. For the qualitative variables, absolute and relative frequencies will be presented. Student’s *t* test, the Mann-Whitney *U* test, Pearson’s chi-square test or Fisher’s exact test according to normality will be used to compare the groups. The linear regression model (quantitative outcomes) and the Poisson regression analysis (qualitative outcomes) will be applied, considering a *p* value of less than 0.20 in the bivariate analysis. A *p* < 0.05 will be considered. The Statistical Package for Social Sciences (SPSS) version 21.0 will be used for analysis.

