It is also considered that the method of this study is robust and adequate to evaluate the effect of educational intervention to family caregivers of the stroke survivors, besides offering important information for the implementation of SHARE in the context of the Brazilian health system. At the moment, the study is in the phase of data collection with an expected end in July 2017.

Possible limitations to this study may include the loss of follow-up due to the death of the stroke survivors, hospitalization in long-term institutions or caregivers exchange, as well as the hiring of formal caregivers. Despite this, the studies developed with this approach in the international context are limited and they are unpublished in the national (Brazilian) context. The present study will contribute to necessary information for future research.

From this RCT it will be possible to provide scientific arguments for the implementation of educational nursing intervention to family caregivers of stroke survivors at home. It is expected that there will be a reduction of the family caregivers’ burden, improvement in their QofL, as well as a decrease in the hospital readmission of the older adults and use of the health services of the stroke survivors and their family caregivers. In addition, this study will provide support for the strengthening of public policies directed to home care and to family caregivers of dependent stroke survivors.

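### Exclusion criterion 3 is not limited to deaths before randomisation, so it contradicts the planned intention-to-treat analysis

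*Protocol article*

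**What the plan says.** The Exclusion criteria section of the protocol article removes a participant if "3) the stroke survivor died during the study". The death criterion has no time limit other than the study itself.

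The order of events is in Recruitment and randomization. Dyads are selected during the hospital stay, then "Participants selected will receive a HV for baseline assessment within 7 days after discharge", and "Randomization will occur after the baseline evaluation of stroke survivors and family caregivers". The final assessment is 60 days after discharge.

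The Data analysis section states an intention-to-treat analysis in which "data from all participants (stroke survivors and their family caregivers) will be used regardless of the time they participated in the study".

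The participants are the caregivers, and the primary outcomes are their burden and quality of life. Readmission of the survivor is a secondary yes/no outcome: "The outcomes of hospital readmission and use of health services will be evaluated 60 days after discharge". The Other outcomes section does not say how a survivor who has died is counted. The Discussion mentions, as a possible limitation, "the loss of follow-up due to the death of the stroke survivors, hospitalization in long-term institutions or caregivers exchange".

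**The concern.** An eligibility rule should be decidable before allocation. This one turns on an event that can occur at any time up to day 60, in either arm and after the intervention has begun. Applied to a randomised dyad, it is a post-randomisation exclusion, and the analysed groups are no longer those that randomisation formed.

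Two kinds of data are at stake. First, a caregiver who is alive, was randomised and could still report quality of life at day 60 leaves the primary analysis because of something that happened to another person. Second, a survivor who is readmitted and then dies leaves both numerator and denominator of the readmission comparison, although fewer readmissions is one of the trial's stated hypotheses. The result could still be reported as intention-to-treat.

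**Working it through.** **The plan's own figure.** The Sample size section gives 0.9 SD, power 0.80, confidence 0.95 and 20% loss. Taking the test as two-sided:

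n per arm = 2 × ((1.960 + 0.842) / 0.9)² = 19.38, rounded up to 20; 20 × 1.2 = 24; total 48.

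The stated 48 reproduces. The sample size is not in question, and this point is about who is analysed.

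**When the criterion acts.** Baseline is by day 7. If randomisation follows at once, at least 60 − 7 = 53 of the 60 days after discharge lie after it. The first intervention visit is due within 14 days, so even a randomisation as late as day 14 leaves 60 − 14 = 46 days. Only deaths between selection and randomisation can be excluded without breaching intention-to-treat.

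**One dyad, three statements.** Take a dyad randomised around day 7 whose survivor dies on day 40:

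- Exclusion criteria: the dyad is excluded.
- Data analysis: its data are used, whatever its time in the study.
- Discussion: the death is a possible loss to follow-up.

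The first two cannot both be followed. The third is compatible with the second and does not cancel the first.

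**What exclusion could do to readmission.** The documents give no rates, so all counts here are assumed. Take 24 per arm and 6 readmitted in each: 6/24 = 25.0% in both, ratio 1.00. If two readmitted control survivors die and are removed, the control arm becomes (6 − 2)/(24 − 2) = 4/22 = 18.2%, and the ratio of intervention to control is 0.250/0.182 = 1.38, against SHARE with no true difference. If two readmitted survivors die in each arm, both become 4/22 and the ratio stays 1.00.

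A second set starts from 6/24 (intervention) and 8/24 (control), a difference of 8.3 points, with every death preceded by a readmission:

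| Deaths removed (intervention, control) | Intervention | Control | Control minus intervention |
|---|---|---|---|
| none | 6/24 = 25.0% | 8/24 = 33.3% | 8.3 points |
| 1, 3 | 5/23 = 21.7% | 5/21 = 23.8% | 2.1 |
| 2, 4 | 4/22 = 18.2% | 4/20 = 20.0% | 1.8 |
| 3, 3 | 3/21 = 14.3% | 5/21 = 23.8% | 9.5 |
| 4, 2 | 2/20 = 10.0% | 6/22 = 27.3% | 17.3 |
| 0, 4 | 6/24 = 25.0% | 4/20 = 20.0% | −5.0 |

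The contrast can shrink, grow or reverse, depending on where a few deaths fall.

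**The case against.** The strongest defence is that the criterion is loosely worded. A death between selection in hospital and randomisation also meets it, and excluding that dyad is legitimate. The intention-to-treat sentence could be read as keeping whatever was collected before a death, and the Discussion's phrase about loss to follow-up fits a dyad that stays in the randomised set with missing data. The first part stands: it would be wrong to say that the criterion can only be met after randomisation. But nothing in the text confines it to the earlier window, and a charitable reading of the Data analysis section does not remove the exclusion stated elsewhere.

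Three stronger readings are tempting and not supported:

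- A reader might infer that the worst readmission outcomes are certain to be removed, in a known direction. No rates are given, and the illustration with a ratio of 1.38 puts both deaths in one arm; an even split gives 1.00. The 20% allowance (9.6 of 48) covers loss from every cause and is no estimate of deaths.
- A reader might infer that dyads are also dropped after institutional care, a change of caregiver or the hiring of a formal one. The Discussion names these only as possible limitations and sets no rule.
- A reader might infer a complete-case analysis. The article does not say so, and handling of missing values may sit in an analysis plan that is not shown.

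**Conclusion.** The point holds as a contradiction within the article: criterion 3, as worded, removes randomised dyads, and the Data analysis section says that all participants' data are used. It reaches the primary outcomes, through the caregivers removed, as well as readmission, function and service use. Its effect on the results cannot be sized from the documents. What can be said is that, with 24 per arm, a few deaths split unevenly between the arms could shift the readmission contrast noticeably, on assumed counts and in either direction. No effect on the caregiver outcomes has been quantified. The conclusion rests on the stated order of baseline, randomisation and day-60 assessment, and on reading the criterion as it is written.

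**What to change.** - Reword criterion 3 so that it covers only deaths before randomisation.
- State that every randomised dyad stays in its allocated arm for analysis, including any already set aside under this criterion.
- Count readmissions and service use that occurred before a death, and report deaths by arm.
- Keep readmission as the stated secondary outcome, and show readmission or death by day 60 as a supporting analysis.
- For a caregiver whose survivor has died, use day-60 quality of life where it can be measured. Say explicitly how burden is treated, and do not impute burden of care after the death as if it were an ordinary missing value.

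The cost is mainly wording in the eligibility and analysis sections, plus one supporting analysis and a table of deaths. The day-60 assessment already exists. Because the Trial status section shows recruitment and intervention under way, the change should be dated and made before the arms are compared. For dyads affected by a death, the date of death and any earlier readmission or service use must be obtained.
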